#### Sample size determination

In the study by Summers et al. (42), the EuroQol 5 dimensions (EQ 5D) was evaluated in two groups of older adults with physical pre-frailty conditions. EQ 5D, a test widely used to measure health status-related quality of life, was used to calculate the sample size. Assuming an overall sample size of 220 subjects (110 cases and 110 controls), 2 repeated assessments (baseline and follow-up), a significance level of 0.05, power of 90%, a correlation among repeated measures of 0.5, and a non-sphericity correction ε of 1 in an ANOVA model within-between interactions, the achieved effect size for this study is 11% (corresponding to a small effect size in a coherent way with the literature). Even factoring in a dropout rate of 10%, the total number needed would be 240 subjects, evenly divided into 120 cases and 120 controls. The hypothesis is that this sample size is more than adequate to detect variations in secondary outcomes. For these secondary outcomes, a treatment effect size is assumed to be similar to or even greater than the one identified for the primary outcome.

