### Outcome measures

All outcomes will be measured following a standardized operating procedure. The primary endpoint of the study is constituted by the improvement in the quality of life after the use of the e-VITA system, to be measured through the EQ-5D-5L, after 6 months of training.

The secondary endpoints encompass: (1) adherence to the coaching intervention, measured by the frequency of technological device usage, and collected through semi-structured interviews and technical data; (2) usability and the user experience of the overall system assessed using the System Usability Scale (SUS) (62) at both the midpoint and the conclusion of the experiments, along with the User Experience Questionnaire [UEQ (63) and UEQ+ (64)] in the middle and at the end of the experiments; (3) improvement in eHealth literacy, to be addressed through the eHealth Literacy Scale (eHEALS) (65), social connectedness through the UCLA Loneliness scale (UCLA) (66), nutritional state through the short version of Food Frequency Questionnaire (FFQ) (67) to estimate the frequency of daily food intake over a period, cognitive status, through Montreal Cognitive Assessment (MoCA) (39), psychological mood through the Geriatric Depression Scale (GDS) (40), functional status through Short Physical Performce Battery (SPPB) (41), participation to leisure activities through an *ad-hoc* checklist; meets the participant’s objectives through ADTPA-5 (scale B and E adapted) (68). A semi-structured interview will be used to complement the information collected by questionnaires, focusing on acceptability, attitude, usability, and cost–benefit analysis; other questionnaires will be used to better understand our participants’ sociodemographics questionnaire, Clinical Frailty Scale (CFS) (38), Big Five Inventory – 10 (BFI-10) (69), and Affinity for Technology Interaction (ATI) (70).

Table 3 presents a concise overview of all collected data and their respective collection time points.

**Table 3 tab3:** Schedule of assessment and outcome measures.

Dimension	Scale	R	T0	T1	T2
Clinical frailty scale	CFS	X			
Cognitive status	MoCA	X			X
Psychological status	GDS	X			X
Physical capacity	SPPB	X			X
Overall health status	Clinical anamnesis	X			
General information	Socio-demographics questionnaire	X			
Quality of life	EQ-5D-5L		X		X
Goals and expectation	ATDPA-5 (Scale B and E)		X		X (Scale B)
eHealth literacy	eHEALS		X		X
Social connectedness	UCLA		X	X	X
Personality	Big Five Inventory – 10 items		X		

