#### Data collected by the researchers

The first step of the data analysis will deal with the description of the sample. Continuous variables will be reported as either mean and standard deviation or median and interquartile range based on their distribution (assessed using the Kolmogorov–Smirnov test). Categorical variables will be expressed as an absolute number and percentage. Comparison of baseline measurements between groups will be evaluated by unpaired t-test (for normal distribution), Mann–Whitney U tests (for non-normal distribution), or chi-square tests (for categorical variables). Within each group, independent and dependent variables will be compared between the pre-conditions and post-conditions using the same tests as appropriate. The treatment effect on the outcome variables will be evaluated by using repeated measures ANOVA, in order to compare the changes over time in the outcome measures between the intervention group and control group. Moreover, a linear regression model on the outcome variation between baseline and follow-up will be estimated in order to evaluate the effect of the treatment adjusted for all potential confounders. For the analysis of the results, the two types of subjects, stratified according to the MoCA cutoff (score ≥ 26 for cognitively healthy subjects, score 22 to 25 for subjects with mild cognitive decline), will be considered separately. Descriptive statistical analyses will be performed on the quantitative data with SPSS or R studio.

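### The results are to be considered separately in two MoCA groups, not labelled as subgroups, while the 90% power holds only for one pooled test

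*Protocol article*

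**What the plan says.** **Sample size (section Sample size determination).** The trial is sized on a single comparison of the two arms: "Assuming an overall sample size of 220 subjects (110 cases and 110 controls"), with "2 repeated assessments (baseline and follow-up"), "a significance level of 0.05, power of 90" per cent, and "a correlation among repeated measures of 0.5, and a non-sphericity correction ε of 1 in an ANOVA model within-between interactions". From these inputs, "the achieved effect size for this study is 11" per cent. Allowing for dropout, "Even factoring in a dropout rate of 10%, the total number needed would be 240 subjects, evenly divided into 120 cases and 120 controls". MoCA does not enter the calculation.

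**Primary endpoint (section Outcome measures).** The endpoint is improvement in quality of life, "to be measured through the EQ-5D-5L, after 6 months of training". It is defined for the enrolled population, without reference to MoCA.

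**Analysis (section Data collected by the researchers).** Treatment effects on the outcomes are to be assessed by repeated measures ANOVA comparing change over time between the arms. A linear regression on the change from baseline, adjusted for potential confounders, is added. The text then turns to the analysis of the results and divides participants at the MoCA cutoff into those scoring 26 or more and those with "score 22 to 25 for subjects with mild cognitive decline), will be considered separately". No word such as subgroup, secondary or exploratory is attached to this division, and the article gives no expected size for either group.

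**The concern.** The two sections do not describe the same test. The sample size is for one group-by-time interaction in everyone. The MoCA sentence, read literally, replaces that with one result per cognitive group, each on only part of the sample.

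If the sentence is followed that way for EQ-5D-5L at 6 months, the trial reports two primary results, both with less power than the article states. The two can disagree, and the question the trial was sized for, whether e-VITA improves quality of life in the enrolled population, is not the one tested. If instead the ANOVA sentence is a pooled primary analysis and the MoCA groups are looked at afterwards, none of this follows. Two competent analysts could work from the same paragraph and produce different primary results.

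**Working it through.** **Inputs from Sample size determination:** N = 220 analysed (110 per arm), k = 2 arms, m = 2 assessments, correlation ρ = 0.5, ε = 1, α = 0.05, and effect size 11%, read as Cohen's f = 0.11.

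**Assumption:** the share of participants in each MoCA stratum is not in the article. I use 50/50, 30/70 and 20/80 of the 220, with equal arms within each stratum and the same f in both.

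**Step 1: reproduce the stated 90%.** For the within-between interaction, power is the upper tail of a noncentral F beyond the 5% critical value, with

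- λ = f² · N · m · ε / (1 − ρ)
- df1 = (k − 1)(m − 1) = 1
- df2 = (N − k)(m − 1) = 218

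λ = 0.0121 × 220 × 2 / 0.5 = 10.648, which gives power 90.1%. The smallest even N that reaches 90% is 220. The stated figure is therefore correct, and it belongs to the pooled sample.

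**Step 2: express the effect as a difference in change.** d = √(4f² · m / (1 − ρ)) = √(4 × 0.0121 × 2 / 0.5) = √0.1936 = 0.44. With ρ = 0.5, the SD of change equals the SD of a single measurement, so this is 0.44 SD. For other values of f, d = 4f. A normal-approximation check with 110 per arm and d = 0.44 gives 90.4%.

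**Step 3: the same test within each stratum.** λ falls in proportion to the stratum size.

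| Assumed split | n in stratum | λ | Power at f = 0.11 | f detectable with 90% power | As a difference in change (4f) |
|---|---|---|---|---|---|
| 50/50 | 110 and 110 | 5.32 and 5.32 | 62.8% and 62.8% | 0.156 and 0.156 | 0.62 and 0.62 SD |
| 30/70 | 66 and 154 | 3.19 and 7.45 | 42.1% and 77.4% | 0.203 and 0.131 | 0.81 and 0.52 SD |
| 20/80 | 44 and 176 | 2.13 and 8.52 | 29.7% and 82.7% | 0.250 and 0.123 | 1.00 and 0.49 SD |

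Even at 10/90 (22 and 198 people) the larger stratum reaches only 86.9%, and the smaller has 16.6%. The chance that both strata are significant is 39.5%, 32.6% and 24.6% for the three splits in the table.

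**Step 4: error rate, conditional on use.** If each stratum were tested at 0.05 and either could support a claim, the two-sided family-wise error over two disjoint groups would be 1 − 0.95² = 9.75%. Counting only false findings in favour of e-VITA, it would be 1 − 0.975² = 4.9%, against 2.5% for one test. Splitting α would control this but lower power further: at 0.025 each and a 50/50 split, power is 51.6% per stratum.

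**The case against.** The best defence is that the ANOVA sentence carries no stratum restriction and matches the test in the sample size section. The aim, the objectives and the primary endpoint are also stated for all participants. A pooled ANOVA followed by results by MoCA group is a plausible reading, and under it the 90% stands. The MoCA sentence itself names no test, no α and no deciding role for either group. This defence holds far enough that one cannot say flatly that the stated power is lost. It does not remove the problem, because the sentence speaks of the analysis of the results without exception and nothing marks it as subordinate to a pooled test.

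Two stronger readings are tempting but not supported:

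- **That the trial gives itself two uncorrected chances of success.** The article is silent on α across the strata. Its Data analysis section promises a comprehensive analysis plan, which is not shown and could settle this. The 9.75% therefore describes one possible use of the two tests, and it includes false findings of harm.
- **That balance within the MoCA groups is unprotected because randomisation is not stratified.** The random sequence described under Technological description of coaches concerns allocation to coaching devices. It does not clearly describe allocation to experimental or control group, so nothing can be concluded from it here.

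**Conclusion.** The conflict is real but conditional. The 90% is a pooled-sample figure, and the article's only statement on how the MoCA groups enter the analysis is that they are taken separately. If that governs the primary outcome, power at the planned effect is about 63% in each stratum at best for the smaller one (equal split), and no split examined reaches 90% in either stratum. If a pooled ANOVA is intended as primary, the 90% holds and only the wording is at fault.

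The size of the loss rests on three assumptions: the stratum shares, an equal effect in both strata, and the article's own f and ρ. The power mismatch does not depend on any multiplicity rule in the unseen plan, whereas the error-rate figures do. The article does not establish an uncorrected error rate as a fact.

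**What to change.** Replace the MoCA sentence with:

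> *The primary analysis includes all randomised participants together, with MoCA stratum (≥26 vs 22–25) as a covariate; one treatment-by-stratum interaction is tested as a secondary analysis, and stratum-specific estimates with 95% CIs are descriptive.*

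This makes the analysis the one that the 220 participants were sized for. It needs no new data and only one added term in the change-score regression already planned. The price is that neither cognitive group supports a confirmatory claim of its own. The interaction test will also be imprecise: at an equal split, the standard error of the difference between the two stratum effects is twice that of the pooled effect (√2 for halving the sample, times √2 for taking a difference).

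The alternative, a confirmatory result in each stratum, would require re-sizing. About 220 analysed per stratum at α = 0.05 means 440 in total, or 440 / 0.9 = 489 enrolled. About 260 per stratum at α = 0.025 each means 520 in total, or 520 / 0.9 = 578 enrolled. The plan is for 240.

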#### Data collected by the technological devices

One of the uses of the data collected from the sensors is to infer the activity of the user and know his or her location so that the voice coach carries out personalized dialogs adapted to the contexts of the user. The environmental data will be used to identify dangerous situations and difficulties and inform the user by giving him the right recommendation to remedy this situation. The aggregation of activity data from several testing centers will serve to motivate users and strengthen their adherence to the experiment. The analysis of user activity data and their interactions at well-defined milestones in the experiment will make it possible to detect system failures as early as possible, in order to prevent the user from dropping out.

### Ethical consideration

The study received approval from the Ethics Committee of the Istituto Nazionale Ricovero e Cura per Anziani (IRCCS INRCA) (CE INRCA 23005), the German Association for Nursing Science (Deutsche Gesellschaft für Pflegewissenschaft e.V.) for the Diocesan Caritas Association of the Archdiocese of Cologne, and the Research Ethics Committee (Comité Ethique de la Recherche) for Assistance Publique – Hôpitaux de Paris. It was registered in ClinicalTrials.gov on 28 April 2023, with the number NCT05835856.

The study will be adhered to regulatory and legal requirements, which were initiated after receiving evaluation and approval from an independent ethics committee and completing administrative requirements at the conducting institution.

Additionally, all potentially eligible participants will receive comprehensive information about the study and must provide consent to participate.

Participants are required to consent to the processing of personal data in anonymous and aggregate form, aligning with EU Regulation 2016/679 (GDPR)/APPI on the protection of individuals and concerning the processing of personal data and Legislative Decree No. 101/2018. The participant must be informed that his or her data may be examined by authorized personnel or members of the competent ethics committee and officials of the competent regulatory authorities;

The participant is also informed and asked to provide *ad-hoc* informed consent to participate in the study, including data retention for up to 10 or 15 years (depending on the country’s rules) after completion of the study.

Each signature must be personally dated by each signatory, and the informed consent and any additional patient information must be retained by the investigator. A signed copy of the informed consent and information sheet will be given to each patient.

Participant information and consent forms are included in the documentation attached to the request for approval by the local ethical committee.

[Optional] The Participant has the opportunity to indicate his or her agreement to the retention and use of his or her data long after the end of the project under the OPEN ACCESS TO SCIENTIFIC PUBLICATIONS AND OPEN RESEARCH DATA as requested by the European Commission.

In the documentation submitted for approval by the IRCCS INRCA Ethics Committee, patient information and consent forms are integral components. These documents play a crucial role in ensuring that participants receive detailed information about the study and have the opportunity to provide informed consent before their involvement. This approach aligns with ethical standards and regulatory requirements to safeguard participants’ rights and well-being.

### Dissemination of research findings

The study findings will be utilized for publication in peer-reviewed scientific journals, contributing to the academic and research community’s knowledge. Additionally, the results will be presented in scientific meetings, fostering discussions and knowledge sharing within the academic and professional spheres. Summaries of the outcomes will be provided to investigators, enabling them to disseminate key findings within their clinics, further promoting the practical application of the study results in relevant healthcare settings.

## Discussion

In the face of an aging population, interventions are needed to reduce or minimize the consequences of various diseases related to advancing age (6), support the healthcare system, and promote active aging, in which the senior is allowed to maintain their autonomy as long as possible. One such solution has been identified in virtual coaches (16) which, through a personalized system that constantly keeps the senior constantly monitored (23) identify situations in which it would be desirable to intervene and propose to the user different solutions and activities adapted to his or her needs and requirements, allowing the person to maintain a healthy and active lifestyle. Despite the advantages that these technologies bring, they also have some limitations: in fact, there are several coaches of this type, but it is obviously necessary for them to be perfectly integrated into the lives of the older adults so that they take into account their real needs that are also due to belonging to different cultures. It is from this premise that the e-VITA project begins, in which different technological devices were proposed to consider people’s actual needs; the present study adopts a randomized, single-blind controlled trial design to enlist healthy older adults aged 65 years and older. Its primary objective is to assess the effectiveness of the e-VITA platform in this demographic. This robust research design allows for rigorous examination and comparison of outcomes, ensuring a comprehensive evaluation of the platform’s impact on the health and well-being of the participants. Participants will be selected from the four sites described above. In this study, the primary goal is to assess the improvement in the quality of life (QoL) of older individuals, which was measured after 6 months. To evaluate the effectiveness of the treatment, the study population will be stratified into two groups. The experimental group will engage with the e-VITA platform, comprising a virtual coach, various monitoring sensors, a smartphone for home use, and a booklet. In contrast, the control group will receive the booklet alone. This design enables a comparative analysis, allowing for the examination of the impact of the e-VITA platform on enhancing the quality of life in older adults. The virtual coaching system will detect daily physical, cognitive, psychological, and social changes in the older person and provide useful advice and recommendations accordingly. In this way, although the primary goal is to improve the person’s quality of life, the system will also act on other dimensions, such as mood, cognitive status, nutrition, social connectedness, and eHealth literacy. In this study, the intervention will be regularly monitored by the research team, which will conduct evaluations in order to ensure its quality. In addition, researchers will be constantly over the call for any doubts or difficulties from users to support their motivation and participation in the trial.

### Limitations

Participants will be selected from the Neurology Operating Unit and the Rehabilitation Medicine Operating Unit of IRCCS INRCA, so the results may not be generalizable to the general population. In addition, the e-VITA system is composed of several types of technological equipment, which could be a limitation for those older adults who, while meeting the inclusion criteria, are not particularly familiar with these types of devices. These problems could be solved by incorporating user-friendly interfaces with clear and intuitive navigation to enhance ease of use. In addition, comprehensive guides and tutorials could be developed to help participants familiarizing themselves with the system. Moreover, users could attend training sessions to be guided through initial set-up and use, to accommodate those who may need further assistance.

## Conclusion

The study aims to introduce users to a cross-cultural and customizable virtual coach, which was designed to address various aspects of the older person’s well-being, including social relationships, physical activity, autonomy, and safety. The ultimate goal is to enhance the overall quality of life for older individuals. To rigorously assess the true potential and identify any potential issues with the intervention, a randomized controlled trial is deemed essential. This research design will provide valuable insights into the effectiveness and challenges associated with the implementation of the virtual coach in improving the well-being of older adults.
